### Sample size calculation

For the determination of sample size, we used G*power [40]. We based calculations on a previous study that used incentives to enhance event-based prospective memory [12]. The effect size in this study (Cohen’s *f* = 0.25) suggests that an inclusion of *n* = 54 participants would be needed to find such effects in a repeated measures design with two groups and five measurements with *α* = 0.01 and a power of 1-β = 0.99. To account for attrition, drop-out or exclusion due to movement artefacts, we plan to recruit *N* = 60 participants (*n* = 30 in each group).

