### Statistical analysis

#### Behavioural: Do loss-related incentives enhance prospective memory?

Since we are primarily interested in whether incentives will enhance prospective memory, we will report accuracy and mean response times for the event-based task as well as accuracy and clock checking for the time-based task as primary outcomes.

First, we will test whether incentives will improve task accuracy. We will use two-way mixed-design ANOVA on correctly remembered trials, with the within-subject factor ‘task type’ (event-based or time-based) and the between-subject factor ‘group’ (incentive or control). Next, we will test whether response times in the event-based task will become quicker with an incentive. We will use one-way ANOVA on response times for correctly remembered trials, with the between-subject factor ‘group’ (incentive or control). For time-based prospective memory, we will test whether an incentive influences how often participants check the clock. Similar to our previous study [36], we will divide the 30 s before and after each target time into four intervals: T – 30 refers to the interval 30 to 15 s and T – 15 to the interval 15 to 0 s before target time. T + 15 or T + 30 then correspond to the intervals 0 to 15 s and 15 to 30 s after the target time. We will use a two-way ANOVA with the within-subject factor ‘time-interval’ and the between-subject factor ‘group’ (incentive or control). Finally, we will test whether monthly income, retirement status, personality traits, reward sensitivity, executive functions, or daily life prospective memory will predict performance. We will use linear regression with prospective memory accuracy as dependent variable and scores from the questionnaires as predictors. Age and gender will be included as covariates in all statistical analyses.

We will use R (Version 4.2.1) with Rstudio (Version 2022.02.3) for statistical analyses, with *p* < 0.05 considered statistically significant. We will correct for multiple comparisons using Tukey’s method. Whenever the assumptions of normality or homogeneity are not met, data will be transformed and/or non-parametric alternatives will be used. In case of missing data, we will use linear-mixed effects models rather than ANOVAs.

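### The stated 0.99 power at n = 54 belongs to a five-measurement within-subject or interaction test that the trial does not run; for the incentive (group) effect, power is about 0.3 (alpha 0.01) to 0.6 (alpha 0.05)

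*Protocol article*

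**What the plan says.** The Sample size calculation section takes its effect size, f = 0.25, from an earlier incentive study of event-based prospective memory. From it the section derives a total of 54, the number that "would be needed to find such effects in a repeated measures design with two groups and five measurements". The error rates behind that number follow in the same sentence: "with *α* = 0.01 and a power of 1-β = 0.99". The section does not name the model term being powered, and it gives no correlation between measurements. To allow for losses, "we plan to recruit *N* = 60 participants (*n* = 30 in each group").

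The behavioural part of the Statistical analysis section states that the primary interest is whether incentives enhance prospective memory. It then fixes three analyses of the primary outcomes:

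- **Accuracy.** The stated aim is that "we will test whether incentives will improve task accuracy". The method is given as "We will use two-way mixed-design ANOVA on correctly remembered trials, with the within-subject factor", which is task type with two levels; group is the between-subject factor.
- **Event-based response time.** A one-way ANOVA on group, with one value per participant.
- **Clock checking.** Four time intervals by two groups.

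The significance level for all of them is set "with *p* < 0.05 considered statistically significant".

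**The concern.** The sample size section fixes one design and the analysis section fixes others. No behavioural outcome is measured at five levels, so the calculation describes a test that is not planned.

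The difference matters because of where the incentive sits in the design. Each participant is either in the incentive group or in the control group, so the question of benefit is answered by the main effect of group. A within-subject or interaction test gains power from repeated measurements and from high correlation between them. A between-group test gains little from repetition and loses power as the correlation rises. Power for one says almost nothing about power for the other.

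At stake is how a null result will be read. In the Discussion, under the heading on whether incentives modulate prospective memory, a finding of no improvement is put down to an ineffective prosocial component, weak loss motivation, ceiling or floor performance, or high intrinsic motivation. Limited power is not listed there or under Limitations. A reader told that power is 0.99 would accept that list. If the true figure is near 0.6, an effect of the assumed size would be missed about 40% of the time.

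**Working it through.** **Inputs from the protocol article.** f = 0.25; k = 2 equal groups; m = 5 measurements, alpha 0.01 and power 0.99 (Sample size calculation). N = 54 needed, 60 recruited. Planned m = 2 for accuracy, 4 for clock checking, 1 for response time; alpha 0.05 (Statistical analysis).

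**Assumptions.** The correlation rho between measurements is not given. I use 0.5 and vary it from 0 to 0.8. Sphericity is assumed. f = 0.25 is taken as the effect on each single measurement.

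**Formulas (noncentral F).**

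- Within factor, or group-by-measurement interaction: lambda = f² × N × m / (1 − rho), df = (m − 1) and (N − 2)(m − 1).
- Between-group effect: lambda = f² × N × m / (1 + (m − 1) × rho), df = 1 and N − 2.

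**Step 1: reproduce the plan's figure.** Within or interaction test, m = 5, rho = 0.5, alpha 0.01:

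- N = 52: lambda = 0.0625 × 52 × 5 / 0.5 = 32.5; power 0.989.
- N = 54: lambda = 0.0625 × 54 × 5 / 0.5 = 33.75; power 0.992.

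With equal groups, 54 is the smallest N that reaches 0.99, so the published number is reproduced exactly.

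**Step 2: try the group effect with the same inputs.** With m = 5, rho = 0.5 and alpha 0.01, the between-group test needs N = 236; its power at N = 54 is 0.39. Even at rho = 0 it needs N = 82. The figure of 54 therefore does not come from the between-group test.

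**Step 3: power of the planned group effect on accuracy (m = 2, rho = 0.5).** N = 54: lambda = 0.0625 × 54 × 2 / 1.5 = 4.5. N = 60: lambda = 0.0625 × 60 × 2 / 1.5 = 5.0.

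| Test, f = 0.25 | alpha 0.01, N = 54 | alpha 0.01, N = 60 | alpha 0.05, N = 54 | alpha 0.05, N = 60 |
|---|---|---|---|---|
| Group effect, accuracy (m = 2, rho 0.5) | 0.30 | 0.34 | 0.55 | 0.59 |
| Group effect, response time (m = 1) | 0.21 | 0.24 | 0.44 | 0.48 |
| Group × task interaction (m = 2, rho 0.5) | 0.84 | 0.88 | 0.95 | 0.97 |
| Group × interval interaction, clock checking (m = 4, rho 0.5) | 0.98 | 0.99 | >0.99 | >0.99 |

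**Step 4: sensitivity of the accuracy group effect to rho, alpha 0.05.**

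| rho | N = 54 | N = 60 |
|---|---|---|
| 0 | 0.72 | 0.77 |
| 0.3 | 0.61 | 0.66 |
| 0.5 | 0.55 | 0.59 |
| 0.7 | 0.50 | 0.54 |
| 0.8 | 0.48 | 0.52 |

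At alpha 0.01 the same range of rho gives 0.48 to 0.24 (N = 54) and 0.53 to 0.28 (N = 60).

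**Step 5: what the claim would require.** For the accuracy group effect at rho = 0.5, N = 292 is needed for power 0.99 at alpha 0.01, and N = 98 for power 0.80 at alpha 0.05. Conversely, at alpha 0.05 the effect detectable with 80% power is f = 0.32 at N = 60 (d = 2f = 0.64) and f = 0.34 at N = 54.

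**The case against.** Several points can be made for the plan.

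- **The correlation is assumed.** It is, and the power depends on it. At alpha 0.05 a fair range is about 0.5 to 0.75. The top of that range needs task scores that are almost uncorrelated, and even 0.77 is far from 0.99.
- **Alpha 0.01 is stricter than the level used.** Correct. Planning at 0.01 and testing at 0.05 is conservative for any one test and does not cause the shortfall. The figures of 0.30 to 0.34 apply only on the planning terms; 0.55 to 0.59 are the ones for the analysis as specified.
- **Age and gender are covariates in every analysis.** Adjustment helps somewhat. If they explained 10% to 30% of the variance of the task mean (an assumption), power at N = 60, alpha 0.05 and rho 0.5 would rise from 0.59 to about 0.64 to 0.75. Reaching 0.80 would take a little under 40%, which nothing in the article suggests.
- **Some planned interactions are well powered.** This stands. Group by interval for clock checking has about 0.98 or more, and group by task has 0.95 to 0.97 at alpha 0.05. These terms ask whether the incentive changes the timing of clock checks, or acts differently in the two tasks. They do not ask whether incentives improve accuracy or response time.
- **The source term for f = 0.25 is not stated.** If it came from a within-subject or interaction term, it may not carry over to a group effect, in either direction. That is a further reason to name the term; it does not support the 0.99.
- **A null would still carry some information.** Also true: the trial has 80% power for d of about 0.64. It is effects of the assumed size, d = 0.5, that it can easily miss.

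**Conclusion.** The concern holds. The sample size arithmetic is correct for a five-measurement within-subject or interaction test, and that test is not in the plan. For the incentive effect on accuracy at f = 0.25, power is 0.55 (N = 54) to 0.59 (N = 60) at alpha 0.05 with rho = 0.5, or 0.48 to 0.77 over rho from 0 to 0.8. At the planning alpha of 0.01 it is 0.30 to 0.34 with rho = 0.5. For response time it is 0.44 to 0.48 at alpha 0.05, whatever the correlation. These figures rest on an unstated correlation, on f = 0.25 applying to each measurement, and on no gain from covariates. No plausible change to these brings the group effect near 0.99. Since this is the article's only power statement and it is wrong for the primary question, it must be corrected.

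**What to change.** Keep N = 60 and rewrite the sample size paragraph:

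1. Name the test being powered: the main effect of group in the 2 (group) × 2 (task type) mixed ANOVA on accuracy, at alpha 0.05.
2. State the assumed correlation between the two task scores, and give power over a range. For f = 0.25 and rho = 0.5 this is 0.55 at N = 54 and 0.59 at N = 60.
3. Give the effect detectable with 80% power: f about 0.32 at N = 60 and 0.34 at N = 54.
4. Report power for the two interactions and for the response-time comparison separately, each with its own number of measurements.
5. Say which term of the earlier study f = 0.25 was taken from.

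In the Discussion, base the reading of a null result on the confidence interval for the group difference, and list limited power among the possible explanations and under Limitations.

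The cost is one rewritten paragraph and a few sentences of Discussion. No analysis changes and no participants are added; the stated power becomes much less favourable.

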### Data management

We will pseudonymise all study data (i.e., participants will be given a unique participant number). The coding key will be stored separately and locked away. Each participant will be informed orally and in writing about the nature, usage, and storage of their data. Behavioural data will be stored in Dropbox folders encrypted with Boxcryptor. Neuroimaging data will be stored on GitLab hosted by servers of Bern University. Paper pencil data will be stored in folders that are locked away. Data processing will be done on personal computers/laptops and institutional servers. All computers will be password-protected and encrypted. The study team will be responsible for data management; data monitoring will be done by an independent researcher not involved in the study. At the end of the study, all personal data will be deleted. The procedures comply with Swiss data privacy laws.

## Discussion

The results of our study will provide insight into three important aspects of prospective memory in older adults. First, our study will reveal whether time-based and event-based prospective memory differ neuroanatomically. Second, we will find out whether we can enhance prospective memory by using an incentive and third, we will determine how incentives are processed in the brain during such tasks.

### What differentiates time-based prospective memory from event-based prospective memory?

Older adults typically perform better in prospective memory tasks in which monitoring demands are low [1, 32, 34, 41]. Time-based prospective memory tasks usually require more monitoring since there is no external reminder of what needs to be done and when. We use a hidden clock in our study and, therefore, our participants need to initiate clock checking by themselves. If participants perform worse in the time-based task compared to the event-based task, we will be able to determine at what point in the task their performance will become affected. It may be that they are well able to monitor the time by checking the clock, but they do not remember the actual intention (i.e., pressing a key when a minute has passed). This would indicate that an execution of many tasks at a time is too demanding for older adults and so they prioritise. Alternatively, they check the clock rather seldomly and therefore, their intentions are not accomplished very timely. This would support previous studies showing that older adults do not check the clock as efficiently as younger adults do and therefore, their time-based prospective memory is less accurate [36, 42]. In addition to dissecting at what point in the task participants’ performance drops, our data will examine the neuroanatomy underpinning time-based and event-based prospective memory. Any differences in brain activity between the two tasks would point to them being related but still biologically distinguishable. A previous study had reported that network activity was similar in time-based and event-based prospective memory [4]. However, it is worth noting that, in that study, the clock in the time-based task was always in plain view while in our study it will need a button press to appear. If hidden, participants may need to manage time similar to real life while a clock always in plain view may rather serve as an event monitor. Thus, we posit that our data will show different brain regions to be involved in either task. If, however, we do not find differences in brain activity between the two tasks, this may indicate that clock visibility in the time-based task does not play a role and that time-based and event-based tasks may activate similar brain areas regardless of the design of the time-based task. In any case, the results of network activity may later be transferred to non-invasive brain stimulation protocols to enhance or inhibit certain brain regions to enhance prospective memory.

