### Prospective memory task

To examine the neural substrates of event-based and time-based prospective memory, we will use a computerized task in the MR scanner [32], which will be presented with PsychoPy (v2021.1.2). The task will consist of four blocks: During the first and the third block, participants will perform a 1-back working memory task (as an ongoing-task), during which they will need to decide whether the current image is the same as the image presented just before (Fig. 2). Pseudorandom sequences of 238 Snodgrass & Vanderwart [33] pictures will be displayed on a screen for 2–3 s, followed by a 1–2 s inter-stimulus interval, used as a temporal jitter. During the second and the fourth block, a prospective memory task will be added to the ongoing task. One block will contain the event-based task and the other block the time-based task. The order will be counterbalanced across participants. In the event-based task, participants are asked to press a button whenever an animal appears on the screen (Fig. 2). Every answer that occurs within 5 s following the presentation of an animal will be considered as a prospective memory hit [32, 34]. In the time-based task, participants are asked to press a button whenever one minute has passed (Fig. 2). To monitor the time, they will be able to press another key to display a clock for 3 s in the upper left corner of the screen. Every correct response occurring ± 2.5 s around each target time will be counted as a prospective memory hit [32, 34]. Each prospective memory block will consist of 158 trials; out of these, 54 trials will be ongoing 1-back hits (i.e., trials in which the picture will be identical to the previous one), and 10 prospective memory cues (i.e., one every minute at 1:00, 2:00, 3:00… until 10:00) so that both tasks are similar. Each prospective memory block will last 10.5 min.

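### The stated time-based outcomes cannot tell a mistimed press from an omitted one, so low accuracy with good clock checking need not mean forgetting

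*Protocol article*

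**What the plan says.** The section on the prospective memory task gives each block "10 prospective memory cues" and defines a hit separately for each task. Event-based: "Every answer that occurs within 5 s following the presentation of an animal will be considered as a prospective memory hit". Time-based: "Every correct response occurring ± 2.5 s around each target time will be counted as a prospective memory hit". In the time-based task the clock is hidden, and a key press will "display a clock for 3 s in the upper left corner of the screen". No category is given for a press outside the window. The legend to Fig. 2 knows only missed events and missed time-points.

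The behavioural analysis section names "accuracy and clock checking for the time-based task as primary outcomes"; response time is planned for the event-based task alone. Accuracy is analysed by "two-way mixed-design ANOVA on correctly remembered trials", with task type within and group between subjects. Clock checks are counted in four 15 s intervals around each target.

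The Discussion section on what differentiates the two tasks says that, if time-based performance is worse, the study can establish the stage at which it suffers. It offers two readings. In the first, participants may be "well able to monitor the time by checking the clock, but they do not remember the actual intention". In the second, they check rarely and so act late.

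**The concern.** The two readings are to be told apart with two measures: the hit count and the clock checks. The hit count treats a press outside the window and no press alike. The clock-check intervals count looks at the clock, not presses. A participant who checks often and presses every minute, but a few seconds off, has forgotten nothing. That participant still shows adequate checking with low accuracy, which is the pattern the first reading attributes to a lost intention.

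The task-type comparison has a related weakness. A press 3 s after a visible animal is a hit; a press 3 s after the target minute is not. A task difference in trials described as correctly remembered can therefore come from timing alone.

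At stake is the Discussion's conclusion that doing several things at once makes older adults drop the intention, and any reading of a time-based incentive effect as better remembering rather than sharper timing.

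**Working it through.** The article gives no figure for this point, so there is none to reproduce. Its sample size calculation is not an input.

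**Step 1: the rules side by side**

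| | Event-based | Time-based |
|---|---|---|
| Reference point | visible cue | uncued minute |
| Hit window | 0 to 5 s after | 2.5 s before to 2.5 s after |
| Width | 5 s | 5 s |
| Latest hit | 5 s late | 2.5 s late |
| Early press | no early side to the window | non-hit if more than 2.5 s early |
| Other outcome | response time | clock checks in 15 s intervals |

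The widths match, but the windows do not make the same demand. Each clock-check interval is 15/2.5 = 6 times the half-window.

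**Step 2: hits for someone who forgets nothing**

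Assume a press for all 10 targets and a normal timing error with mean b and SD s (both assumed).

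Expected hits = 10 × p, where p = Φ((2.5 − b)/s) − Φ((−2.5 − b)/s)

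| Mean error b | s = 1 s | 1.5 s | 2 s | 3 s |
|---|---|---|---|---|
| 0 s | 9.9 | 9.0 | 7.9 | 6.0 |
| 1 s late | 9.3 | 8.3 | 7.3 | 5.7 |
| 2 s late | 6.9 | 6.3 | 5.9 | 5.0 |
| 3 s late | 3.1 | 3.7 | 4.0 | 4.0 |

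Example: b = 0, s = 2 gives p = Φ(1.25) − Φ(−1.25) = 0.789. So 21% of remembered presses fall outside the window. At s = 1, 1.5 and 3 s the share is 1%, 10% and 40%.

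**Step 3: share of non-hits that are mistimed presses**

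Assume in addition that 85% of targets are remembered.

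Share = 0.85(1 − p) / (1 − 0.85p)

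- b = 0, s = 2: 0.85 × 0.211 / (1 − 0.85 × 0.789) = 0.180/0.330 = 54%.
- b = 1, s = 2: p = 0.733, so 0.85 × 0.267 / (1 − 0.85 × 0.733) = 0.227/0.377 = 60%.

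**Step 4: effect on the task-type comparison**

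The simulation used 60 people and 10 targets per task. Remembering was equal in both tasks, with a mean of 85% that varied between people as Beta(8.5, 1.5). Event presses were never late. The task types were compared by a paired t-test at two-sided 0.05, over 4000 runs.

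| Timing error | Comparisons significant |
|---|---|
| b = 0, s = 1 s | 8% |
| b = 0, s = 1.5 s | 95% |
| b = 0, s = 2 s | 100% |
| b = 0, s = 3 s | 100% |
| b = 1 s, s = 1 s | 75% |

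The test compares hit accuracy, so these are not false rejections of its own hypothesis. They show how often a task difference appears although remembering is equal.

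**The case against.** The case on the other side is substantial.

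- **The Discussion text is hedged.** It offers possible readings, and late execution is one of them. A reader might infer a fixed rule that classes individual participants as having forgotten. The article has no such rule: it sets no threshold for adequate checking, and the analysis section draws no such inference. What remains is that the ability to locate the failure is stated without hedging, and lateness is tied only to rare checking.
- **Timeliness is part of the construct.** The Background defines time-based prospective memory by acting at a specific time, and earlier work is cited for the windows. This stands: the hit score is a legitimate measure of timed performance. It does not license attributing every non-hit to forgetting.
- **Press times are used.** A reader might infer that no planned analysis looks at when the press occurred. That goes too far: hit scoring depends on press times, and the fMRI regressors are built on the onsets of correct answers. Only presses outside the window go unanalysed.
- **The primary question is the group comparison.** A reader might infer that the incentive effect is biased. The documents do not support this, because both groups are scored with the same window.
- **Good monitors may time well.** They can call up the clock on demand, so large errors are less plausible for them, and at SD 1 s without bias the problem nearly vanishes. This is fair, but the stated outcomes would not show which case applies.
- **Detail may sit in an analysis plan not shown.** It may. The point here is that the outcomes the article does state cannot carry the inference it also states. The post-scan description of the task does not fill the gap, because it tests knowledge of the instructions rather than action at each target.

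**Conclusion.** The point holds as a limit on interpretation. For participants who check often but press outside ±2.5 s, the stated outcomes cannot distinguish a mistimed press from an omitted one, so reading their low accuracy as a lost intention could be wrong. The task-type difference mixes remembering with timing precision for the same reason. The incentive comparison within the time-based task is sound as timed performance; only its reading as better remembering is affected.

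The size is conditional. The shares of 1% to 40% rest on an assumed normal timing error with mean zero. The share of non-hits that are mistimed and the simulation also assume 85% remembering, and the simulation assumes that event presses are never late. The effect is negligible at SD 1 s without bias and large from about 1.5 s, or with 1 s of systematic lateness. That an out-of-window press counts as missed is inferred from the absence of any third category.

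**What to change.** - Keep the ±2.5 s hit score as the primary accuracy measure.
- From the press times, add a secondary classification of each time-based target: on time; mistimed (a press nearest that target, outside ±2.5 s but within a bound stated in advance); or omitted. The 15 s width already used for clock checks is one candidate for the bound.
- Report this classification and the timing error by group.
- Repeat the task-type comparison on non-omitted targets as a sensitivity analysis.
- Base any statement that the intention was not remembered on omissions only, and any statement about untimely execution on the mistimed class.

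The cost is a scoring script on press times that hit scoring already needs, plus one extra analysis, with no new procedure for participants. The downside is one more secondary measure and a bound that has to be chosen before the data are examined.
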